## Abstract

**Background:**

Even though the effectiveness of lifestyle modifications and antihypertensive pharmaceutical treatment for the prevention of hypertension and its complications have been demonstrated in randomized controlled trials, the benefits of adhering to these treatments have not been popularized among the general public. Studies suggest that incentive approaches based on behavioral economic concepts can improve patients’ adherence to treatment. Therefore, we aimed to test whether financial incentives will reduce the blood pressure (BP) of hypertensive patients in China.

**Methods/Design:**

This is a multicenter, randomized controlled trial with two parallel arms. A total of 400 participants from six cities in the Liaoning and Shanxi provinces of China are block-randomized into intervention and control group with a 1:1 ratio. Patients in the control group will receive interactive management of mobile devices, including patient education and communication. Patients in the intervention group will receive financial incentives in addition to interactive management of mobile devices, conditional on them achieving their antihypertensive goals or hypertension control. Masking the arm allocation will be precluded by the behavioral nature of the intervention and investigators of BP measurement and statistics are masked to clinic assignment. The primary outcome is net change in systolic BP (SBP) from baseline to month 12 between the intervention and control groups. The secondary outcomes are net change in diastolic BP (DBP), BP control, change in medication adherence and lifestyle, and cost-effectiveness.

**Discussion:**

This trial will determine whether financial incentives will improve hypertension control and generate necessary data for controlling hypertension and concomitant cardiovascular diseases among hypertensive patients in China.

**Trial registration:**

ISRCTN13467677. Registered on 16 May 2019.

## Background

Hypertension is a global public health challenge and a major modifiable risk factor of cardiovascular disease (CVD) and premature death [1]. It has been estimated that 7.6 million premature deaths—54% of stroke and 47% of coronary heart disease worldwide—are attributable to hypertension [2]. In 2013, a study of 17 countries showed that the prevalence, awareness, and control of hypertension were 40.8%, 46.5%, and 32.5%, respectively [3]. The hypertension situation in China is also urgent. Results from the China Hypertension Survey 2012–2015 show that 23.2% (an estimated 244.5 million) of the Chinese adult population (aged ≥ 18 years from 31 provinces in mainland China) had hypertension, 46.9% were aware of their diagnosis, 40.7% were taking prescribed antihypertensive medications, and 15.3% had controlled hypertension [4]. From 2004 to 2015, the total cost of hospitalization for acute myocardial infarction, intracranial hemorrhage, and cerebral infarction reached RMB 153.40, 231.99, and 52.426 billion [5]. Therefore, controlling hypertension has become the top priority in the prevention and treatment of chronic diseases in China.

Several lifestyle-related interventions have been recommended for the prevention and treatment of hypertension. These include weight loss, a diet including lower sodium and higher potassium intake, increasing physical activity, smoking cessation, and reducing excessive alcohol intake [6]. Pharmaceutical antihypertensive treatment can significantly reduce the risk of major CVD events and death [7–10]. Although the effectiveness of antihypertensive treatment and lifestyle modification in the prevention and treatment of hypertension and its complications have been validated in previous studies, this beneficial effect has not been maximized in the general population [6, 11, 12]. The control of hypertension, especially in developing countries, remains insufficient. Medication adherence is an important factor in poor control of hypertension [11]. Therefore, encouraging hypertensive patients to positively change unhealthy lifestyles and to promote regular medication intake is an important challenge that needs to be addressed in current hypertension control. There is an urgent need to identify innovative strategies to improve the treatment compliance of hypertensive patients, further improve the control of hypertension, and reduce the burden caused by hypertension and its complications.

The effectiveness of financial incentives have been validated in many studies. In 2009 [13] and 2016 [14], researchers from the United States and Switzerland found that the rates of smoking cessation in the incentive group were significantly higher than that in the control group. A randomized controlled trial (RCT) concerning financial incentives for weight loss found that participants in both incentive groups lost significantly more weight than participants in the control group. This suggests that incentive approaches based on behavioral economic concepts could have a major impact on reducing the incidence of obesity-related illnesses [15]. Sen et al. used a RCT to test the effectiveness of financial incentives for improving adherence to remote-monitoring regimens among patients with poorly controlled diabetes and concluded that participants in the incentive group had higher monitoring rates, relative to the control group [16]. In 2013, a cluster RCT of hypertension care in the United States also showed that individual financial incentives resulted in greater blood pressure (BP) control or appropriate response to uncontrolled BP [17].

Financial incentives incorporate the principle of behavioral economics. Behavioral economics combines psychology and economics to study how human psychology influence individuals’ decisions concerning economic activities. Loss aversion refers to the tendency to be more motivated to avoid losses than achieve similarly sized gains [18]. The regret theory suggests that people’s choice will be affected by expectations of regret or disappointment; this anticipated regret has been shown to affect a variety of preventive behaviors [15].

Based on the above, we aim to determine whether financial incentives will reduce the BP of hypertensive patients in China. All interventions, including interactive management of mobile device and financial incentives, have been validated in previous studies on hypertension control or other disease indicators. This study will generate the necessary data for controlling hypertension via financial incentives and promoting it on a larger scale will be considered if meets the cost-effectiveness principle.

### Objectives

The overall aim of this study is to explore whether financial incentives will reduce the BP of hypertensive patients’ in China. The specific aims of this RCT are:
To test whether financial incentives will lower systolic BP (SBP) and diastolic BP (DBP) among hypertensive patients over a 12-month period, compared to the control group;To evaluate whether financial incentives will increase the control rate of hypertension among hypertensive patients over a 12-month period, compared to the control group; andTo estimate the cost-effectiveness of this intervention program compared to control group.

## Methods

### Research design

This study is a multicenter RCT. A total of 400 hypertensive patients from six cities in the Liaoning and Shanxi provinces of China will be recruited. Of these, 200 participants will be assigned to the intervention group and 200 participants to the control group by block randomization. The financial incentives will last for 12 months (Fig. 1). The primary outcome is the net change in SBP from baseline to month 12 between the intervention and control groups. We will also conduct health economic analysis and consider promoting it on a larger scale if meets the cost-effectiveness principle.

**Fig. 1 Fig1:**
[figure not shown]
Study design of the project

### Study population

Patients of this trial will be selected from six cities in Liaoning and Shanxi provinces in China. The institutions for selection include Shengjing Hospital of China Medical University, Fushun Mining General Hospital of Liaoning Health Industry Group, Dandong Central Hospital, Anshan Central Hospital, Fuxin Mining General Hospital of Liaoning Health Industry Group, and Fenyang Hospital of Shanxi Medical University. The inclusion and exclusion criteria for the study population are listed below.

The inclusion criteria are as follows:
Aged 35–75 years;Hypertensive patients (SBP/DBP ≥ 140/90 mmHg during two separate screening/baseline visits);Have WeChat and use it skillfully;Local residents who have been living in the city for > 12 months;Voluntarily joined and signed informed consents.

The exclusion criteria are:
Pregnant women or women who are planning to become pregnant during the next year;Patients with plans to move from their place of residence during the next year;Individuals with malignant tumors or severe liver or kidney dysfunction;Secondary hypertension patients.

All study participants meeting the inclusion and exclusion criteria will be additionally assessed by a trusted member of the staff.

The research protocol was approved by Shengjing hospital of China Medical University Medical Ethics Committee (No. 2019PS397K) and written informed consent was signed by all the participants or their guardians during screening.

### Randomization and blinding

Patients will be block-randomized to the intervention and control groups in a 1:1 ratio by an independent statistician using a computer-generated randomization list. The randomization will take place after the patients have been enrolled. The randomization is stratified by geographic regions and the number of stratification is 6. Due to the behavioral nature of the intervention, patients and principle investigators will not be blinded to patient allocation. However, investigators responsible for BP measurement and statistics will be masked to clinic assignment. The details of the randomization will be kept confidential until completion of data analysis.

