### Intervention

We will explore whether financial incentives will reduce the BP in hypertensive patients in China. Participants in the control group will receive interactive management of mobile devices, including the following:
Patient education: researchers will send relevant knowledge concerning prevention and treatment of hypertension at the beginning of each week using WeChat, including the definition and severity of hypertension, methods for correctly measuring BP, lifestyle-related hypertension prevention, the types and selection of antihypertensive drugs, and the harmful effects and complications of hypertension.Communication: if the patients have any questions during the intervention and follow-up, they can communicate with the researcher through the mobile at any time and the researcher will answer their questions.

Patients in the intervention group will receive financial incentives in addition to interactive management of mobile devices. The specific measures include two parts:
Participants will be encouraged to self-measure BP once a week and record the condition of antihypertensive medications. A reward of RMB 5 (red envelope) per participant will be awarded if they record the results accurately and completely every week.At the follow-up months 1, 3, 6, and 12, researchers will measure participants’ BP and give a reward of RMB 50 or an equivalent gift (shopping cards, phone bills, cooking oil, etc.) to the patients whose BP values were decreased by 10 mmHg (compared to their baseline BP values) or achieve the control criteria (SBP/DBP < 140/90 mmHg).

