Each of the BP measurements will be obtained by study nurses who are masked to clinic assignment and measurement will be according to the standard protocol recommended by the American Heart Association [19]. BP will be measured with the participant in a seated position after 5 min of quiet rest. Additionally, participants will be advised to avoid alcohol, cigarettes, coffee/tea, and exercise for at least 30 min before their BP measurement. At the same time, the condition of antihypertensive medications will also be asked before measurement. BP is measured three times on one day with a 1-min interval and the mean of six BP values was calculated and used for all subsequent analysis. BP was measured using a standardized automatic electronic sphygmomanometer (HEM-8102A; Omron, Tokyo, Japan) and one of four cuff sizes (pediatric, regular adult, large, or thigh) will be chosen on the basis of each participant’s arm circumference.

Anthropometric measurements were measured with participants wearing light clothing and without shoes by investigators using a standard protocol. Three measurements will be obtained at each visit for weight, height, waist circumference, and hip circumference; the arithmetic means will be used for analyses.

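### Masked BP assessment is intended but not secured: masking is stated for the clinic rather than the patient's arm, and two sections disagree on who measures BP

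*Protocol article*

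**What the plan says.** **Unit of allocation.** Research design states that "200 participants will be assigned to the intervention group and 200 participants to the control group by block randomization". Randomization and blinding says the same at patient level: "Patients will be block-randomized to the intervention and control groups in a 1:1 ratio by an independent statistician". It adds that "The randomization is stratified by geographic regions and the number of stratification is 6", so region is a stratification factor and not the thing allocated.

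**Masking.** Patients and principal investigators are declared unblinded to patient allocation. The next sentence says that "investigators responsible for BP measurement and statistics will be masked to clinic assignment". The Abstract (Methods/Design) has "Masking the arm allocation will be precluded by the behavioral nature of the intervention and investigators of BP measurement and statistics are masked to clinic", where the next word is again assignment. Data collection repeats the idea: "Each of the BP measurements will be obtained by study nurses who are masked to clinic assignment".

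**Who measures and who pays.** The Intervention section states that "Patients in the intervention group will receive financial incentives in addition to interactive management of mobile devices". For follow-up months 1, 3, 6 and 12 it says that "researchers will measure participants’ BP and give a reward of RMB 50 or an equivalent gift". The reward is conditional on a 10 mmHg fall from baseline or on reaching the control criterion.

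**Primary outcome.** Study outcomes defines it as the between-group difference in SBP change from baseline to month 12.

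**The concern.** Patients know their arm, so masking of the people who take the readings is the main stated protection for the primary outcome. Two features of the text weaken it.

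- The masking is described against a unit that was never randomised. With 1:1 blocks within each stratum, every region contains both arms. Not knowing a clinic's assignment therefore gives no protection against knowing a patient's arm.
- One section combines measurement and reward in the same group of staff, and the reward exists in one arm only. A person who does both tasks cannot be masked to arm.

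Month 12 is both the primary time point and a rewarded visit, so the gap reaches the primary endpoint as well as the interim visits. If assessors did know the arm, the likelier direction of bias would be towards the intervention.

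**Working it through.** This is mainly a comparison of sections. The arithmetic in step 5 only gives scale.

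**1. Is there a clinic assignment to mask?** Research design gives 200 patients per arm. Randomization and blinding gives patient-level blocks, 1:1, in six strata, a number that matches the six hospitals listed under Study population. Both arms are present in each stratum, so no clinic has an assignment.

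**2. Is masking to the patient's arm stated anywhere?** The masking of assessors is described in three places: the Abstract, Randomization and blinding, and Data collection. All three refer to the clinic. The Abstract also says that masking of arm allocation is precluded, without limiting this to patients and principal investigators as the main text does. Arm-level masking of assessors is stated nowhere.

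**3. Who takes the readings?**

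| Section | Who measures BP | Stated masking | Gives the reward? |
|---|---|---|---|
| Intervention | researchers | none stated | yes, intervention group only |
| Data collection | study nurses, for every measurement | to clinic | not mentioned |

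Taken at face value, the two rows cannot both describe arm-masked measurement. The second does not cure the first, because its masking is also only to clinic.

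**4. Does this touch the primary endpoint?** Month 12 is listed as a rewarded visit under Intervention and as the primary time point under Study outcomes. Yes.

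**5. Scale, under an assumption.** Inputs: 200 per arm (Research design); SD 20.0 mmHg, target difference 7.0 mmHg, two-sided 0.05 and 90% power (Data analysis and statistical power).

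- Plan's own figure: n = 2 × (1.960 + 1.282)² × 20² / 7² gives 172 per arm, 344 in total. With 200 per arm the power is 93.8%. The planned 400 would equal 344 / (1 − 0.14), that is, an assumed 14% loss which the article does not state. The difference is on the conservative side and has no bearing on masking.
- Standard error of the difference: 20 × √(2/200) = 2.0 mmHg.
- With no true effect and a differential measurement bias b, the rejection rate is Φ(b/2.0 − 1.96) + Φ(−b/2.0 − 1.96).

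| Assumed b (mmHg) | Share of 7 mmHg | Two-sided false-positive rate |
|---|---|---|
| 0 | 0% | 5.0% |
| 1 | 14% | 7.9% |
| 2 | 29% | 17.0% |
| 3 | 43% | 32.3% |

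The values of b are assumptions. Nothing in the document supports one row over another, and zero is possible. The table also treats 20 mmHg as the SD of the analysed quantity and ignores missing data and the mixed model.

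**The case against.** A reader might infer that the primary outcome is in fact assessed by unmasked staff. The document does not support that, for four reasons.

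- In Randomization and blinding, the masking sentence is set in contrast to the sentence on those who know patient allocation. The contrast makes best sense if assessors are masked to the same thing, so clinic may simply be the wrong noun. The same section keeps randomisation details confidential until the analysis is complete.
- Data collection is the section devoted to measurement, and it names masked nurses for every reading.
- The Intervention section uses researchers loosely, for those who send education, answer questions, measure and pay. It may mean the whole team, with nurses measuring and others paying.
- The procedure is tightly described: an automatic device, five minutes' rest, three readings a day one minute apart, the mean of six values, and cuff size chosen by arm circumference. These are not free choices for the assessor.

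A second tempting inference is that the assessor gains from a low reading. The reward goes to the patient, and the Discussion describes incentives as aimed at participants and not providers. No assessor benefit is stated.

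All of this stands, and it is why the point is limited to masking that is not secured. It does not remove the point. Intent inferred from a contrast is weaker than a statement of what is masked, and the same wrong unit appears in all three descriptions. A fixed procedure on an automatic device reduces the room for bias but cannot rule out departures by someone who knows the arm. Condensation into an article explains omitted detail; it does not explain a wrong unit or two sections that name different measurers.

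**Conclusion.** The point holds in a limited form. The plan intends masked BP assessment but does not secure it. Masking is stated for a unit that is not allocated, masking to the patient's arm is stated nowhere, and the Intervention and Data collection sections conflict on who measures BP at visits that include the primary time point.

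The defect in wording and the conflict can be read directly from the text and rest on no assumption. That bias will actually occur does not follow from the text, and its size cannot be derived. The rise from 5% to about 8% for a 1 mmHg bias shows only that a modest bias would matter when the standard error is 2.0 mmHg; it is not an estimate for this trial. What is needed is a correction of wording and roles, not a redesign.

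**What to change.** 1. In the Abstract, in Randomization and blinding, and in Data collection, replace the reference to clinic assignment with the participant's allocated arm. In the Abstract, limit the statement that masking is precluded to patients and principal investigators, as the main text does.
2. Reconcile Intervention with Data collection. Masked study nurses take and record all BP readings, identically in both arms. Existing unmasked staff who do not measure BP then determine and deliver the reward from the recorded values. The study coordinator mentioned under Safety monitoring and assessment could do this if that person takes no readings.

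**Cost.** Changed wording and a reordering of tasks among existing staff. The reward reaches the patient slightly later. Sample size, power and the primary analysis are unchanged. An unmasked patient can still reveal the arm to a nurse, so some risk remains.

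One could go further by settling the month-12 reward on the first day's readings and analysing the second day's separately. I would treat that as optional. Both days involve the same patients and possibly the same staff, so the comparison would not isolate assessor bias.

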### Intervention

We will explore whether financial incentives will reduce the BP in hypertensive patients in China. Participants in the control group will receive interactive management of mobile devices, including the following:
Patient education: researchers will send relevant knowledge concerning prevention and treatment of hypertension at the beginning of each week using WeChat, including the definition and severity of hypertension, methods for correctly measuring BP, lifestyle-related hypertension prevention, the types and selection of antihypertensive drugs, and the harmful effects and complications of hypertension.Communication: if the patients have any questions during the intervention and follow-up, they can communicate with the researcher through the mobile at any time and the researcher will answer their questions.

Patients in the intervention group will receive financial incentives in addition to interactive management of mobile devices. The specific measures include two parts:
Participants will be encouraged to self-measure BP once a week and record the condition of antihypertensive medications. A reward of RMB 5 (red envelope) per participant will be awarded if they record the results accurately and completely every week.At the follow-up months 1, 3, 6, and 12, researchers will measure participants’ BP and give a reward of RMB 50 or an equivalent gift (shopping cards, phone bills, cooking oil, etc.) to the patients whose BP values were decreased by 10 mmHg (compared to their baseline BP values) or achieve the control criteria (SBP/DBP < 140/90 mmHg).

### Study outcomes

The primary outcome is net change in SBP, defined as the difference between the intervention and control groups from baseline to follow-up months 12. Secondary outcomes include net change in DBP, the proportion of hypertension control (BP < 140/90 mmHg), changes in self-reported medication adherence, body mass index (BMI), physical activity, counselling frequency, counselling content, number of steps in WeChat, pulse wave velocity (PWV), ankle brachial index (ABI), and cost-effectiveness among all participants.

